## Randomization

Ibis Reproductive Health produced a randomization scheme to assign women to one of the two study groups based on a permuted block randomization design based on randomly assigned block sizes of 8, 10 and 12. The randomization scheme is stratified by study site. When each woman enrolls, field staff open the next sealed, opaque, numbered envelope at that site to reveal the study group to which the woman will be assigned. Staff do not open the envelopes until a woman is ready to be enrolled to avoid manipulation of the randomization scheme. Each woman’s group and randomization number are be noted on relevant study forms and in the study register.

## Product Administration Plan

At enrollment, women randomized to the diaphragm group are fitted for diaphragm size and receive an Ortho All-Flexdiaphragm. Staff also instruct women about how to use the Replens gel and how to properly clean and store their diaphragms and gel applicators***.***

To improve diaphragm compliance during the trial, only women who are able to correctly insert the diaphragm are enrolled into the study. In order to avoid introducing a bias between the study arms, all women practice diaphragm insertion *before* they are randomized. Women who are not able to correctly insert/remove the diaphragm after five attempts are not eligible to enroll into the study. Following randomization, women in the diaphragm arm will receive condoms, a diaphragm and gel, and more counseling. Women in the condoms-only arm receive condoms and counseling and are told that they can receive a diaphragm to keep and use as they wish at the end of their participation in the study.

Throughout the study, we encourage women to return to the study site if they experience any problems using the diaphragm or would like further instructions or advice. We also ask women to return to the clinic or mobile site at any time during the study if they feel discomfort. A clinician provides a larger- or smaller-sized device as needed. Women who have a vaginal delivery during the study are re-fitted for diaphragm size. As part of ongoing quality assurance processes, there are systematic checks of diaphragm fittings, which sometimes result in a woman being fitted with a new diaphragm size. Replacements for damaged or lost diaphragms can be obtained in the clinic at any time during the study or can be distributed through home visits when compatible with confidentiality requirements.

Women are instructed to insert the diaphragm at any time before sex. We ask them to put lubricant gel in the dome and rim of the diaphragm at the time of insertion and to reapply gel in the vagina before each act of vaginal sex. We ask them not to cleanse the vagina or the diaphragm immediately after sex but to leave the device in place for at least 6 hours. Staff also instruct women about how to properly clean and store their diaphragm and gel applicator. Women are allowed to resume normal vaginal hygiene after sexual intercourse (*i.e.* cleanse outer genitalia with water or water and soap) as long as they do not remove the diaphragm within six hours after sex.

As stated earlier, women in both study arms receive safer-sex counseling and are offered free male condoms. Condoms dispensed by the study are unlubricated or have a non-spermicidal lubricant. The number of condoms women receive is based on expressed need, and if a participant runs short of condoms, she can come to the study clinic at any time to obtain more. While condom use will be promoted throughout the trial, women who indicate that they will not use condoms will not be required to take condoms home with them.

At closing, all women in both arms of the study are eligible to receive a diaphragm, plus a supply of Replens gel to last through the end of the study (May 2007).

## Product Supply and Accountability

Once received at the study site, all supplies will be stored in a secure, limited-access area. Clinic staff will account for all supplies received and dispensed, and at the end of the study, may then destroy or otherwise dispose of surplus supplies as agreed upon with UCSF.

UCSF will outline the product-related responsibilities of each site, including procedures for adequate and safe receipt, handling, storage, and dispensing of diaphragms, lubricant gel and condoms. This includes product accountability records that must be kept to document supplies received and dispensed to study participants.

## Compliance Counseling and Assessment

Compliance counseling is provided to study participants upon enrollment and at every visit thereafter to help ensure high rates of product use. Counseling is provided in accordance with a standard manual that addresses such topics as client-centered strategies to remember to use study products for each episode of vaginal intercourse, ensure the availability of the products both in the home and away from home, and to negotiate product use with “primary” and “non-primary”’ partners. For participants who have adherence problems, every effort is made to identify adherence strategies to increase their rates of product use throughout the course of the study. We record diaphragm, gel and condom use at each quarterly follow-up visit.

In an effort to improve validity of self-reported sexual behavior and compliance data, we use Audio Computer Assisted Self Interviews (ACASI). ACASI has been shown to increase reporting of sensitive behaviors due to perceived increased confidentiality and privacy and has been found feasible in developing country settings. The Population Council tested ACASI at two South African trial sites during a Phase II microbicide trial and found that it was feasible and highly acceptable to trial participants, including those of low literacy.30 Similarly, in Zimbabwe in a recent study where women of reproductive age were randomized into an ACASI or face-to-face interview about reproductive health issues, the majority of women in all educational groups said that it was easy to understand the recorded questions, that they were very comfortable entering their responses into the computer, and that they preferred ACASI to in-person interviews, especially when answering questions about sexual behavior.

Face-to-face interviews provide our main data on demographics, medical history, acceptability, and clinical assessments. The ACASI program includes questions that are particularly sensitive, such as questions about diaphragm and gel use, condom use, and other sexual behaviors such as numbers of partners and anal sex. Experience has shown that diary data do not provide accurate estimates of use in this type of study population.29 Using ACASI, we ask women whether they use study products “every time,” “more than half the time,” “less than half the time,” or “Never” to be able to distinguish measures of effect among perfect users, never users, and estimates of a dose response for users in-between. Together with our TAC, we have been monitoring compliance rates over time and adherence-counseling methods have been updated to address lower-than expected rates.

# 9 Study Procedures

## Scheduled Visit Summary

There are seven to eleven scheduled visits over one to two years depending on the participant’s time of entry into the study including:

- Screening visit
- Enrollment visit
- Product and safer sex counseling visit at 2 weeks post-enrollment
- 4-8 quarterly visits post-enrollment through months 12 to 24 (closing visit)[[1]](#footnote-2)

Unscheduled interim and post-trial visits take place when desired by a participant or by the study staff to follow-up on adverse events (AEs), to provide test results, for re-supply of study products, or for other reasons associated with trial participation.

We will conduct exit focus group discussions and in-depth interviews with a sub-sample of participants and their male partners after women complete the trialto further assess the acceptability of diaphragm and gel use. Volunteers will go through a separate consent process before participating in the focus group discussions. Specific procedures to measure acceptability will be developed.

## Recruitment and First Contact

Study sites recruit women from family planning and general health clinics, through community-based organizations, through word-of-mouth in the community, by postering and leafleting in strategic areas, and by advertising in the general media if necessary. These methods have proven successful in existing studies in each site.

Study staff approach potentially eligible women at recruitment sites and ask them if they are interested in learning more about a diaphragm trial in which they may be able to participate. Recruitment and educational materials are used to convey the key aspects of the trial to potential participants, such as study objectives, inclusion and exclusion criteria, study procedures including random assignment to a study arm, diaphragm and condom use, enrollment exam and laboratory testing, the visit schedule, and study risks and benefits. All materials used for recruitment and education of potential participants are reviewed by the UCSF Committee on Human Research and by other relevant local and US-based IRBs.

If a potentially eligible woman expresses interest in trial participation, she is given an appointment for screening at one of the study clinics.

## Screening Visit

Screening is a step-wise process, beginning with questioning about inclusion and exclusion criteria using a standardized eligibility checklist and ending with laboratory and clinical assessments. These laboratory and clinical procedures only take place after the participant has given written informed consent for screening. Study staff obtain oral consent from the potential participant before administering the checklist, maintain privacy and confidentiality, and do not document the participant’s name or any other personal identifiers on the checklist.

A study staff member reviews the Screening Informed Consent Form with the potential participant and provides further information as needed. If the potential participant wants to join the study and the staff member feels confident that the woman understands they both sign the Screening Informed Consent Form. If the participant is illiterate, either her representative or a witness who is not a member of the study staff may sign the consent form in her place. Alternatively, a thumbprint together with the signature of the study staff member who gave the information about the study and obtained consent can be used.

The following procedures take place:

- Oral consent to complete eligibility checklist obtained.
- Eligibility Checklist completed. Women who are not eligible based on the checklist complete their study participation at this point.
- Written screening informed consent.
- Short questionnaire on demographics and condom use.
- Pre-test counseling for HIV and other STIs.
- Urine specimen for *Chlamydia trachomatis*, *Neisseria gonorrhoeae*, and *Trichomonas vaginalis* testing.
- Fingerstick (or venipuncture) for blood sample to do OraQuick[[2]](#footnote-3) and Determine®c rapid HIV testing.
- HIV results notification.
- Post-test counseling for both HIV-positive and HIV-negative women.
- Women who have inconsistent HIV rapid testing results (one positive and one negative result) at screening will have a venipuncture to collect a blood sample for confirmatory laboratory ELISAe testing.
- Scheduling of results/enrollment visit within two weeks post-screening.
- Collect locator information.

All procedures are performed by qualified, trained study staff. Staff are free to provide additional services to study participants or to refer them to appropriate services for any reproductive health complaint.

Women can refer their male partners for testing and counseling for HIV and other STIs at any point during the study. Male partners of women identified with laboratory-confirmed *Neisseria gonorrhoeae*, *Chlamydia trachomatis*, or *Trichomonas vaginalis* are notified according to national partner notification guidelines. Care and support for women who test positive for HIV at screening or during the trial is outlined in Section 9.10.

UCSF, the laboratory monitor, and the medical advisor on this protocol developed clinical procedures that include instructions on urine collection, OraQuick and Determine® rapid HIV testing, PCR and other STI diagnostic tests, and performing pelvic exams. They also developed guidelines for the treatment of STIs and vaginal infections, clinical and psychosocial referrals, clinical management of safety endpoints and AEs, universal precautions, and quality control of clinical procedures. Each site modified these procedures and guidelines according to local circumstances. In addition, each site developed a site-specific accidental exposure to blood or body fluids procedure and a partner notification procedure.

We provide all participants with the name and telephone number of the local principal investigator and a study staff member who speaks their language in case they have any questions about the study. In the event that a participant has questions or concerns about her rights as a study participant and would like to discuss them with a non-study staff member, all participants are given the name and telephone number of a member of the local IRB as an independent source of information.

## Enrollment Visit

For the majority of eligible women (*i.e.* those who do not need confirmatory HIV testing) the enrollment visit takes place within two weeks after the screening visit. Women who have inconsistent HIV tests at screening and require confirmatory testing also return to the clinic to receive their HIV results. Those with negative confirmation results may then enroll provided they return to the clinic within two weeks.

Women who return to the clinic for their enrollment visit greater than two weeks but within 30 days of their screening visit have repeat HIV testing. If HIV-negative and otherwise eligible, they can be enrolled into the trial.

For women who do not enroll within 30 days of their screening visit, repeat screening procedures including HIV and STI testing are completed and they are asked to return to the clinic within two weeks for enrollment. We give participants the results of the laboratory tests performed at the screening visitat their enrollment visit*.*

The following additional procedures take place at the enrollment visit:

- STI test results notification. Women who needed confirmatory HIV testing due to inconsistent results at screening are given their results.
- Post-test counseling.
- Treatment of women who tested positive for CT / NG / TV at screening visit and, when compatible with confidentiality requirements, provision of referral testing and treatment services to their partners.
- Review of eligibility checklist to confirm eligibility.
- Review of screening questionnaire.
- Written informed consent for main study.
- Urine specimen for pregnancy testing. Urine sample is stored for future testing. Pregnant women complete their study participation at this point.
- UTI diagnosis. Urine specimen for culture is only collected if a woman is symptomatic and has a positive dipstick urinalysis. Women who are treated for UTIs may still be enrolled.
- ACASI baseline questionnaire.
- Pelvic exam with speculum and inspection of vagina and cervix solely to determine presence of a healthy cervix for eligibility.
- Assessment of any signs noted by clinician during pelvic exam or symptoms self-reported by participant of STIs and reproductive and urinary tract infections. If women are diagnosed with a current STI/RTI and it is treatable at the visit, they can be administered treatment and continue with the enrollment process.
- Pap smears are provided as an optional service for women.
- Following fitting procedures, the clinician fits the participant with as many sizes as deemed necessary before determining a final diaphragm size.
- Instructions on use, including insertion and removal techniques are provided to the participant. A study clinician supervises diaphragm insertion and removal. Only women who are able to insert and remove the diaphragm are eligible. Women are provided with education and given five attempts to correctly insert and remove the diaphragm. The clinician collects all diaphragms after removal.
- Venipuncture for blood sample is used for TP and HSV-2 testing. Blood samples from all women are stored for future testing.
- Blood of HIV-negative women is used for later PCR testing of timing of infection for those participants who test positive for HIV at the month 3 visit.
- Randomization to one of the two study groups.
- Distribution of Ortho All-Flex® diaphragms and Replens® gel to all applicable women, with instructions on use, including insertion and removal techniques.
- Safer-sex counseling and distribution of male condoms to all women.
- Instructions on available resources for minor or moderate medical problems or emergencies.
- Administration of the Informed Consent Quiz form that assesses a participant’s understanding of the informed consent process and retention of that information.
- Scheduling of two-week visit.
- Update of locator information.

We attempt to minimize social desirability bias throughout the study by interviewing participants about sexual behaviors before counseling them about safer sex and/or by having different staff members interview and counsel each woman at each visit, depending on preferences and feasibility at each study site.

**9.4a Two-week Follow-up Visit**

All women return to the clinic two weeks after enrollment to receive any laboratory results and for product and safer sex counseling. The procedures are as follows for women in both groups:

- Notification of laboratory results and treatment for positive results.
- Post-test counseling.
- Short questionnaire on study product use.
- Safer-sex counseling and distribution of male condoms to all women.
- Brief diaphragm counseling for applicable women, including assessment and problem-solving of difficulties with using the diaphragm, re-supply of gel and replacement diaphragm if damaged or lost to participants in the diaphragm group.
- Scheduling of 3-month follow-up visit.
- Update locator information.

## Quarterly Follow-up Visits

After enrollment, women return quarterly for the duration of their participation in the trial (at the end of months 3, 6, 9, 12, 15, 18, 21 and 24). The visit schedule and procedures will be identical for women in both study arms.

At each follow-up visit, participants undergo the following procedures:

- Follow-up interview—short interview about compliance and sexual behavior at every visit, longer interview including acceptability assessment during the month 3 and month 24 visits or closing visit if it is before 24 months.
- Urine specimen for pregnancy, CT, NG, and TV testing; urine sample is stored for future testing.
- UTI diagnosis: urine specimen for culture is only collected for laboratory testing if a woman is symptomatic and has a positive dipstick urinalysis. Women who are treated for UTIs may continue to use the study products.
- HIV and STI pre-test counseling.
- Venipuncture for blood sample to be used for HIV, HSV-2, and TP testing (TP testing only done at closing visit). Blood samples from all women will be stored for future testing.
- Blood of HIV-positive women (seroconverters) will be used for later PCR testing to determine timing of HIV infection.
- Women who were HSV-2 negative at enrollment are tested again at month 24 visit or closing visit if it is before 24 months. Stored blood samples collected at quarterly visits from women who are HSV-2 positive at closing are tested to determine timing of HSV-2 infection.
- OraQuick and Determine rapid HIV testing.
- HIV results notification.
- HIV and STI post-test counseling for both HIV-positive and HIV-negative women. Samples from women who have positive or inconsistent HIV results undergo confirmatory laboratory ELISA testing.f
- Reminder to participants to return to the study clinic if they experience discomfort, abnormal discharge or other symptoms, or to the nearest clinic/hospital in case of a medical emergency.
- Safer sex counseling and distribution of male condoms to all women who accept them. Brief diaphragm counseling including assessment and problem-solving of difficulties with using the diaphragm, re-supply of gel and replacement diaphragm if damaged or lost to participants in the diaphragm group.
- Administration of Informed Consent Quiz form at 12-month visit or closing visit if it is before 12 months.
- Scheduling of next follow-up visit.
- Update locator information. Exiting participants will be asked for updated contact information and to sign a form indicating their permission or not to contact them after their participation in the trial is completed in order to inform them about trial results, inquire about study product use experience, and/or to participate in future trials.

Women only receive a pelvic exam when clinically indicated. Instructions for complete documentation of AEs and SAEs appear in Section 11. If a women tests positive for HIV or STIs, or if any other abnormalities are found, we provide treatment as outlined in Sections 9.8 and 9.10.

Women may participate and be followed in the study for up to 24 months.

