## Unscheduled Visits

We encourage participants to return to the clinic at any point if they feel there is a problem or if they need additional supplies. If participants report for unscheduled visits, an evaluation of the problem is undertaken and any necessary treatment provided. Findings are recorded on the appropriate study forms.

The following procedures take place at unscheduled visits:

- Notation of last use of diaphragm, gel and condoms.
- Notation of reason for interim visit:
- If for AE or SAE or re-evaluation of previous AE or SAE, appropriate physical exam procedures are conducted as necessary or participant is referred for appropriate medical follow-up. Each AE is documented on an Adverse Event Form and each SAE on a Serious Adverse Event Form (see Section 11).
- If for interim HIV counseling and testing in response to presumed exposure to HIV and/or symptoms of acute infection, counseling and testing are provided as needed.
- If to receive results of laboratory tests, results and treatment are provided as appropriate.
- If to obtain a replacement diaphragm or more gel or male condoms, supplies are provided as needed and recorded on product accountability records.
- If to ask questions or discuss problems with study protocol, guidance is provided as needed.
- Remaining visit schedule is confirmed and changes made as needed
- Locator information is updated

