## 11.2 Product Interruption and Discontinuation

Active participation in the trial, including use of the diaphragm and/or gel, may be discontinued for any of the following reasons:

- The participant withdraws her consent. Participants may withdraw from study participation at any time, for any reason, without loss of any services to which they may be entitled outside of study participation.
- The participant develops a medical condition that is incompatible with the protocol or the clinician determines it to be in the best interest of the participant to discontinue study product use.
- The participant develops an SAE that may be related to study product use.
- Study staff determine it to be in the best interest of the participant for a non-medical reason.
- UCSF, Ibis Reproductive Health, South African MRC, the University of Zimbabwe, PHRU, the Zimbabwe and South African Ministries of Health, the DSMB, or any relevant IRB or regulatory authority halts the study at one or more site(s).

Women who acquire an STI or a vaginal infection may continue to use the diaphragm and gel. In the event of significant genital ulceration, genital lesions with epithelial disruption, or severe generalized erythema, the participant may also continue to use the diaphragm and gel if she wishes and the clinician agrees. These symptoms are picked up routinely through questions about gynecological symptoms and complaints during regularly scheduled study visits. Re-evaluation visits are scheduled at the discretion of the study clinician until healing or resolution is documented. If the condition does not improve after one or more re-evaluation visits with continued diaphragm and gel use, product use may be interrupted until healing or resolution has been documented. Diaphragm and gel use may then be restarted, if doing so is considered safe by the study clinician. If the condition reappears, permanent discontinuation is considered.

The study clinician, in consultation with the local co-PI and/or another study physician, is responsible for deciding whether temporary or permanent discontinuation of diaphragm and gel use is warranted. Every effort is made to complete all protocol-specified visits and procedures for women whose diaphragm and gel use has been discontinued. Diaphragm and gel use may be restarted at any time, if doing so is considered safe by the study clinician and after consultation with a physician as needed).

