The DSMB report will consist of open and closed sections. The open section will be made widely available, including to all study investigators, who may choose to share the report with IRBs, donors, and other interested parties. This section will include data in aggregate form (*i.e.* not broken down by study arm), focusing on trial conduct issues such as overall accrual and drop-out rates, eligibility rates and reasons for ineligibility, baseline characteristics and condom use, and compliance with protocol procedures, including diaphragm use. The closed sectionof the DSMB report will be made available to DSMB members only. This section will include the above data reported by trial arm and data concerning trial endpoints—such as HIV and STI incidence and rates of adverse events—overall and by trial arms and clinical sites.

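### Section 9.5 calls follow-up procedures identical by arm, but section 8.3 adds fit checks and refits only diaphragm women can have; genital adverse events first found there should be identifiable

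*Protocol*

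**What the plan says.** Section 9.5 says of the quarterly visits: "The visit schedule and procedures will be identical for women in both study arms". The same section says: "Women only receive a pelvic exam when clinically indicated". Its own procedure list, however, contains an item for the diaphragm group: "Brief diaphragm counseling including assessment and problem-solving of difficulties with using the diaphragm", together with re-supply of gel and replacement devices.

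Section 8.3 says that, as part of quality assurance, "there are systematic checks of diaphragm fittings, which sometimes result in a woman being fitted with a new diaphragm size". It adds: "Women who have a vaginal delivery during the study are re-fitted for diaphragm size". It gives no frequency for the checks, no share of women to be checked, no visit at which they occur, no description of what the clinician does and no rule for recording findings.

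Section 11.1 defines an adverse event broadly, irrespective of relation to product, and has the on-site clinician judge relatedness and severity. On genital ulceration, lesions and erythema, section 11.2 says: "These symptoms are picked up routinely through questions about gynecological symptoms and complaints during regularly scheduled study visits". No difference between arms is stated for those questions. Under section 12.6 the closed DSMB report gives endpoint data and adverse event rates "overall and by trial arms and clinical sites".

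**The concern.** A reader of section 9.5 would conclude that the arms are observed alike after enrollment. Section 8.3 shows that they are not: one arm has clinician contacts that symptoms do not trigger and that have no stated equivalent in the control arm. A check made on schedule gives an added opportunity to notice or be told of a genital problem. If such findings are entered as adverse events, part of any excess in the diaphragm arm could reflect more looking rather than more harm.

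This matters because the DSMB sees rates by arm and, under section 12.6, may recommend early termination on safety grounds. Participants and clinicians know the assignment. Nothing in the protocol marks an event as first found at a fit check, so the DSMB could not tell how much of a difference came by that route.

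**Working it through.** The protocol gives no adverse event rate, detection rate or fit-check frequency, so there is no stated figure to reproduce. The check is mainly a comparison of texts.

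1. **Who can have the contact?** Fit checks and refits (section 8.3) presuppose a diaphragm in use, so during follow-up they can apply only to the diaphragm arm.

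2. **Is the contact triggered by symptoms?** Section 8.3 calls the checks systematic and places them under quality assurance. Refitting follows delivery. Neither depends on a complaint.

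3. **Does this conflict with section 9.5?** In part. The sentence on identical procedures concerns quarterly visits, and section 8.3 does not say that checks take place there. But the list in section 9.5 itself contains a diaphragm-group item, so the word cannot be literal. The pelvic examination rule also sits uneasily with an unprompted check if that check involves an examination, which the protocol does not say.

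4. **Could a finding become an adverse event?** Under section 11.1 it could. The definition is wide, and the rule on recurrences in section 11.1.2 mentions signs as well as symptoms. No text says that findings at fit checks are recorded, and none says they are not.

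5. **Is there a route common to both arms?** Yes: the symptom questions in section 11.2. Fit checks would add a second route in one arm.

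6. **Can the size be bounded?** Let *s* be the share of genital findings that surface by the common routes in both arms. Let *x* be the share of the remainder that surfaces, and is recorded, at fit checks or refits in the diaphragm arm. With no true difference between arms, the apparent ratio of diaphragm to control is

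   R = [s + (1 − s)x] / s = 1 + x(1 − s)/s.

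   All values below are assumed; none comes from the protocol.

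   | s | x = 0 | x = 0.10 | x = 0.25 | x = 0.50 |
   |---|---|---|---|---|
   | 0.8 | 1.00 | 1 + 0.10 × 0.25 = 1.025 | 1 + 0.25 × 0.25 = 1.0625 | 1 + 0.50 × 0.25 = 1.125 |
   | 0.5 | 1.00 | 1 + 0.10 × 1 = 1.10 | 1 + 0.25 × 1 = 1.25 | 1 + 0.50 × 1 = 1.50 |

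   The table shows only that the answer depends wholly on *s* and *x*, about which the protocol says nothing. No entry is evidence of actual bias.

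**The case against.** The strongest reply is that the conflict is slight. The sentence in section 9.5 is about quarterly visits and is visibly not literal. Symptom questions and endpoint specimens show no difference between arms. Section 12.6 specifies no formal test of adverse events, and tabulation by mode of detection could be left to an analysis plan. All of this stands, and it keeps the point small. It does not dispose of it, because an analysis plan cannot separate events whose source was never captured. Section 9.6 does record the reason for an unscheduled visit, but its listed reasons do not name a fit check.

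Three stronger readings are tempting and are not supported.

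- *A fit check is a vaginal examination of symptom-free women.* Section 8.3 does not describe its content, and section 9.4 lists the enrollment speculum examination and the diaphragm fitting as separate items. That a check involves some examination is a plausible inference, not a stated fact.
- *Only diaphragm women are examined without symptoms.* The HPV sub-study (Appendix 16.2) is offered to the Zimbabwe cohort without restriction by arm. It includes clinician-collected swabs at month 12 and at exit, the latter during a pelvic examination. Unscheduled visits are also open to everyone.
- *STI endpoints are biased because infections treated between quarterly visits go uncounted.* Section 9.6 does say that "an evaluation of the problem is undertaken and any necessary treatment provided", and its list names no chlamydia, gonorrhea or trichomonas specimen. But section 11.1.2 treats laboratory-diagnosed infections as endpoints whether found at a scheduled or an unscheduled visit, and no passage describes presumptive treatment after a fit check.

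**Conclusion.** The texts do not fit together: section 9.5 presents follow-up as the same in both arms, while section 8.3 gives diaphragm women additional clinician contacts. These can bring more genital adverse events to light in that arm, to an extent that is unknown and possibly negligible. The conclusion assumes that at least some genital findings at these contacts are entered as adverse events and would not otherwise have surfaced; the protocol neither confirms nor excludes this. It does not show that events are in fact over-detected, and no rate ratio should be cited as the size of the effect.

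The scope is safety reporting only. Detection of HIV and the STI endpoints rests on blood and urine tests and does not depend on fit checks. Severity is minor, and the change is a cheap improvement.

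**What to change.** 1. Reconcile sections 8.3 and 9.5. Limit the statement of identical procedures to endpoint testing and routine symptom questions, and name fit checks and refits as additional diaphragm-arm contacts. State their frequency, coverage and content, and how they stand against the pelvic examination rule. Which clinical rule applies is for the investigators to settle.
2. Record for each genital adverse event whether it was first found at a fit check or refit. Use a field on the Adverse Event Form, or derive it from visit type if these contacts are logged as such.
3. Report genital adverse event rates by arm with and without those events. Keep every event in the main safety table, so that a real device-related lesion seen at a fit check is not removed from view.

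The cost is one form field and one extra table. No additional specimen or test is needed.
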